### Power

A sample size of 600 participants (n=200 per group) will have sufficient power to detect a change in the primary outcome variable of at least 0.6 median serves/day of EDNP (discretionary) foods (or equivalent to a 360 kJ/day reduction) between groups at 90% power and 5% level of significance. Assuming a drop-out rate of 20%, a total of 600 participants will be recruited.

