### Dietary Assessment

For the face-to-face (active control and tailored feedback) groups, diet will be recorded using the mFR app with inclusion of a fiducial marker (an object of known shape, size, and color) [26] in the image to aid in portion size estimation. “Before eating” and “after eating” images of all foods and beverages consumed over four consecutive days, including one weekend day, will be captured at baseline, 6 months, and 12 months for each participant. In addition, at 6, 12, 18, and 24 weeks, the tailored feedback group will complete a 1-day mFR to encourage self-monitoring of food intake to facilitate feedback. All images will be automatically uploaded to a secure cloud server residing on the Curtin University Bentley campus via Wi-Fi or 3G/4G network. All images will be assessed by a research dietitian for serves of fruits, vegetables, and energy-dense nutrient-poor (EDNP) foods and beverages according to the Australian Guide to Healthy Eating standard serves (one serve=600 kJ) [45].

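### The Power paragraph gives 600 both as the size that has 90% power and as the number recruited under 20% drop-out, so the allowance has no effect as written

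*Protocol article*

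**What the plan says.** The Power section has two sentences. The first reads "A sample size of 600 participants (n=200 per group) will have sufficient power to detect a change in the primary outcome variable". It sets the target difference at "at least 0.6 median serves/day of EDNP (discretionary) foods (or equivalent to a 360 kJ/day reduction" and the operating characteristics as "between groups at 90% power and 5% level of significance". The second reads "Assuming a drop-out rate of 20%, a total of 600 participants will be recruited".

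Other sections show what 600 counts. The Abstract allocates 200 to each of three conditions. The Randomization section sends 200 to online control and 400 to the face-to-face arms. So 600 is the number randomised. An evaluable number, such as 480 in total or 160 per arm, appears nowhere.

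Two further places bear on the paragraph. On the outcome, the Dietary Assessment section says "For the face-to-face (active control and tailored feedback) groups, diet will be recorded using the mFR app", and it describes the scoring of EDNP serves from those images. On the analysis, the Statistical Analysis section compares change between two groups by analysis of covariance and reports an adjusted mean difference with a 95% CI.

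**The concern.** A drop-out allowance should separate two numbers: those who must be analysed and the larger number who must be recruited. Here both are 600. Either the 90% was calculated for 200 analysed per arm and the allowance was never applied, or it was calculated for 160 per arm and the first sentence quotes the inflated number as if it were the powered one. Both cases call for a correction, but a different one.

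This is the only power statement in the article, and it concerns one of the primary outcomes. A result showing no difference in EDNP intake would be judged against 90% power for 0.6 serves/day. A reader should be able to see how many analysed participants that claim rests on.

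**Working it through.** **Inputs from the article.** Difference 0.6 serves/day; power 90%; significance level 5%; 200 per group; drop-out 20% (all from Power). The serve size is "one serve=600 kJ" (Dietary Assessment), so 0.6 × 600 = 360 kJ, which agrees with the article's own conversion.

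**Assumptions, because the article does not state them.** Two-sided test; unadjusted comparison of two means; equal arms. No SD is printed, so the 600 cannot be reproduced directly. The formula is solved backwards for the SD that each interpretation implies.

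**Formulas** (normal approximation):
- SD for 90% power: SD = δ / [(1.960 + 1.282) × √(2/n)]
- Power: Φ( δ / [SD × √(2/n)] − 1.960 )
- Recruitment: n / (1 − 0.20)

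**Interpretation A: 200 analysable per arm are needed.**
- Implied SD = 0.6 / (3.2415 × √(2/200)) = 0.6 / 0.3242 = 1.85 serves.
- Recruitment needed = 200 / 0.8 = 250 per arm, 750 in total.
- With 200 recruited, 200 × 0.8 = 160 remain.
- Power at 160 = Φ(3.2415 × √(160/200) − 1.960) = Φ(2.899 − 1.960) = Φ(0.939) = 82.6%.
- Difference detectable at 90% = 0.6 × √(200/160) = 0.67 serves/day, about 403 kJ instead of 360 kJ.

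A two-sample t calculation gives the same result: standardised difference 0.325, SD 1.85, power 82.6%, detectable difference 0.67. A one-sided test gives 83.5%. The 83% depends on the premise that 200 analysed per arm give 90%. Given that premise the SD cancels.

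**Interpretation B: 600 already includes the allowance.**
- 600 × 0.8 = 480, which is 160 per arm, and 480 / 0.8 = 600 exactly.
- Implied SD = 0.6 / (3.2415 × √(2/160)) = 0.6 / 0.3624 = 1.66 (1.65 with the t distribution).
- Power at 160 is 90%, so there is no shortfall.
- Taken at face value, 200 analysed per arm would then have Φ(3.2415 × √(200/160) − 1.960) = Φ(1.664) = 95%, not 90%.

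**Power for 0.6 serves/day over a range of assumed SDs:**

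| SD (serves) | 200 analysed per arm | 160 analysed per arm |
|---|---|---|
| 1.5 | 97.9% | 94.7% |
| 1.6 | 96.3% | 91.8% |
| 1.65 | 95.3% | 90.2% |
| 1.7 | 94.2% | 88.4% |
| 1.8 | 91.5% | 84.6% |
| 1.85 | 90.0% | 82.7% |
| 2.0 | 85.1% | 76.5% |

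The 90% survives 20% drop-out only if the SD is about 1.66 or less. The two implied SDs differ by only 0.2 serves, and nothing in the article favours one over the other.

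**The case against.** The strongest defence is that both sentences can be true. If 600 is the recruited number with the allowance built in, 480 complete, and those 480 may carry the 90%. The arithmetic is exact, and it fits the use of 200 per group elsewhere as the number allocated. This defence stands. A reader might infer that the trial fails to deliver its stated power, or that the two sentences cannot both hold. The article does not support either inference, because the shortfall exists only under interpretation A. What the defence does not remove is the printed text: the first sentence still attaches the power to 600, and no evaluable number is given.

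Four further objections limit the point.

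- **Missing SD.** A condensed article commonly leaves this to the full protocol, so its absence is not a fault in itself. Here it only means that a reader cannot tell which interpretation applies.
- **Covariate adjustment.** The baseline value is among the possible covariates and could recover some power. The Power section claims no such gain, and the article gives no correlation from which to estimate one.
- **Number of arms.** A reader might conclude that the powered outcome does not exist in online control, so that the comparison rests on 400 rather than 600. That is true only of serves from the mobile food record. Table 1 gives an online food frequency questionnaire to all three groups, and the Power section names no instrument. The per-arm power is the same either way.
- **Median and mean.** It is tempting to relabel the 0.6 as a mean difference. If the calculation was done on medians, that would misreport it.

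**Conclusion.** The Power paragraph is internally inconsistent about whether 600 is the number before or after the drop-out allowance, and it must be corrected. Under the literal reading, power after 20% drop-out is about 83% for 0.6 serves/day, or 90% for about 0.67 serves/day. Under the alternative, 90% holds at 160 completers per arm and only the number in the first sentence is wrong. These figures rest on a two-sided 5% test, an unadjusted comparison of two equal arms, and SDs back-solved at about 1.85 and 1.65 serves. Even in the less favourable case the loss is moderate: about 7 percentage points of power, or 0.07 serves/day in the detectable difference.

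**What to change.** Retrieve the original calculation and rewrite the paragraph per arm: 200 randomised, 160 expected evaluable, and the power that 160 delivers.

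- If 200 analysable per arm was the basis, state about 83% power for 0.6 serves/day, or 90% for about 0.67.
- If 160 was the basis, state 90% power at 160 evaluable per arm and say that 600 includes the allowance.

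Say that, for EDNP serves from the mobile food record, the comparison is tailored feedback versus active control. Reconcile the effect given as a median with the adjusted mean difference in the Statistical Analysis section, using the inputs of the original calculation rather than relabelling the 0.6.

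The cost is a change of wording and possibly a less favourable stated power. No extra participants are needed.

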## Results

Enrollment commenced in August 2017. Primary outcomes at 12 months will be available for analysis from September 2019.

## Discussion

### Overview

Improving participation and reach is a challenge for population-based obesity interventions. Worldwide participation rates in population studies are declining [59], and while enrollment in studies involving face-to-face recruitment is somewhat higher [59], there is a need to evaluate the effectiveness of digital interventions that include multiple strategies to improve engagement [60]. Interventions utilizing digital technologies may have greater appeal in overweight and obese populations, as participants may feel more comfortable completing self-reported questionnaires in a more anonymous setting [61].

Reasons for the lack of adherence to lifestyle recommendations are poorly understood. One contributing dietary factor may be that many adults incorrectly believe their diet to be healthy when it is not [62]. This mismatch between perceived and actual intake may be corrected by more accurate, objective dietary assessment; comparison with national recommendations; and clear, relatable tailored feedback. Furthermore, despite sustained public health efforts, the majority of Australian adults are “inactive,” failing to meet the recommended PA guidelines [63]. Thus, focus on the most-effective messaging strategy (both content and delivery) to target these behaviors is needed. A systematic review of tailored interventions and the identified lack of objective measurements in studies on dietary and PA behaviors are key limitations of tailored interventions [17]. This, in part, is due to difficulty in undertaking more objective methods of dietary and PA assessment on a large scale. Exploring digital methods of assessment may allow more cost-effective approaches to be implemented.

Tailoring focuses on characteristics unique to the person with the intention of improving behavioral outcomes by making the message more acceptable to each individual. Characteristics of messages and feedback that can be tailored include personal behaviors, psychosocial characteristics, and diet and PA behaviors [54]. Personal relevance is key, and dynamic (ongoing assessment) tailoring versus static tailoring (one baseline assessment) has stronger effects over time [15]. Effective tailoring strategies include multiple intervention contacts and iterative feedback [19]. Of note, tailoring may be more effective for men than women [64].

Numerous behavioral theories have been used as a basis for tailored interventions, including the Stages of Change Model and Precaution Adoption Process Model [19]. However, there is increasing support for self-determination theory in weight control, diet, and tailored PA interventions to address autonomous motivation and self-regulation [52,53,65-68]. Central to the self-determination theory is an emphasis on autonomous behaviors (originating from one’s-self), as opposed to pressure or coercion into a particular course of action when delivering advice [67]. This provides a framework for the style of communication to be used in tailored interventions but does not address approaches used in digital technology interventions. Researchers have raised concerns about the lack of models to inform design of technology-based behavioral interventions [20,21]. In response, Mohr et al [20] proposed a behavioral intervention technology framework for interventions that use a range of technologies, including mobile phones, the Web, and sensors aimed at changing behavior. Features such as usability and willingness to continue to use the app may contribute to enhanced participant engagement and motivation [20]. Michie et al [68] developed the COM-B model, which guides researchers to identify behavioral targets and subsequent psychological theories for behavior-change interventions. The COM-B model identifies capability, opportunity, and motivation as the three core categories to perform a behavior. This means that to perform a behavior, individuals must be capable with physical and mental ability (eg, nutrition knowledge and cooking skills) as well as practical and social opportunities (eg, access to affordable and healthy food). Motivation includes automatic drivers like habits as well as goals, beliefs, plans, and impulses. Assessing these determinants is the first step to identify interventions and theories that can help change behavior.

With respect to PA, wearable technology is being rapidly adopted, with over one-third of the Australian population using activity monitors to record PA and sedentary behaviors [69]. These devices are becoming vital in the context of research to facilitate monitoring of activity in real-time and under free-living conditions. Nonetheless, a gap exists between recording/self-monitoring and behavioral change. Furthermore, there is a lack of strongly designed studies that have considered the combination of behavioral theory with activity monitors to improve health behaviors. New-generation activity monitors allow for critical information to be harnessed from large-scale research studies. In this study, activity monitors will be used to record 24/7 behavior, specifically active and sedentary minutes; exercise intensity; nonsedentary hours; and step count in overweight adults. Together with dietary analysis, curation of these data will enable provision of detailed, richer feedback to participants and may therefore be more effective in helping change diet and PA behaviors. If found successful, the approach used in this study could be incorporated into larger-scale health campaigns.

### Conclusions

The current obesity epidemic is occurring against a background of a decline in PA participation and increasingly poor dietary choices, with the incidence of both obesity and prevalence of inactivity worsening with age. Promoting and maintaining healthy diet and PA behaviors through personalized tailored feedback is feasible, novel, and potentially cost effective. Personalized feedback with comparison to recommendations and guidance in forming healthy habits is essential to overcome existing barriers to lifestyle change. Digital technologies (mobile apps, email, and web) have the potential to reach larger populations of healthy adults and those at risk of chronic disease but to date have not been fully explored. The outcomes of this intervention may have the potential to positively impact health at a boarder population level, with findings informing translation of “best practice” lifestyle intervention aimed at overweight adults.

## Abbreviations

BMI: body mass index
COM-B: Capability, Opportunity, Motivation, and Behaviour
EDNP: energy-dense nutrient-poor foods
mFR: mobile food record
MVPA: moderate-to-vigorous physical activity
OC: online control
PA: physical activity
RCT: randomized controlled trial
SMS: short message service
TF: tailored feedback
